### Interventions

The standard of care for the treatment of locally advanced rectal cancer is TME. In patients with cT2N+, cT3N0, and cT3N+ mid-rectal tumors, the administration of nCRT, as well as the direct TME, are both considered guideline-concordant standard treatment approaches and are widely practiced [11,12]. In this study, data from patients undergoing TME as part of routine medical care will be collected prospectively. No additional interventions, treatments and follow-up protocols outside of standard care will be implemented. At the end of the study, patients will be categorized into two groups based on whether they received nCRT and the two groups will be compared in terms of primary and secondary endpoints. No treatment or monitoring protocols differing from routine practice will be proposed for patients or surgeons in the study. The natural prognosis of the treatment arms will be observed.

All the patients undergoing TME described as a precise dissection of the rectum along with the surrounding mesorectal tissue and all pararectal lymph nodes are eligible for the study [13].

**Direct TME Group:** Patients who undergo direct TME without neoadjuvant treatment.

**nCRT Group:** Patients who receive nCRT prior to TME.

Neoadjuvan CRT treatments include all conventional chemoradiotherapy regimens or total neoadjuvant chemoradiotherapy regimens (standard short or long course radiation and/or any standard chemotherapy regimen) described in European and American guidelines [11,12]. The details of radiotherapy and chemotherapy treatments will be recorded, including dosage, frequency, duration, complications, completion status, and the waiting period between treatments. Routine follow-up information for all patients including morbidity, radiologic assessments, recurrence, mortality be recorded in the database for the first five years post-surgery. Patient-reported quality of life scales will be recorded at baseline (prior to the initiation of treatment) and subsequently at 1, 3, and 5 years.

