### Trial design

The CANO trial is a prospective, non-randomized, observational, cohort study. Patients undergoing TME will be included in the study, with a comparative analysis between those receiving neoadjuvant chemoradiotherapy and those who do not. The design precludes any possibility of cross-over between the groups.

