#### Exclusion criteria.

cT4 tumors assessed by MRIStage IV disease assessed by MRI and/or CTPatients with MSI (+) in TME pathologyPatients who received neoadjuvant immunotherapyEmergency surgeryClinical obstructionPrevious pelvic radiotherapyPatients treated without a multidisciplinary council decisionInflammatory bowel diseases (Crohn’s disease, Ulcerative colitis)Familial adenomatous polyposis (FAP), attenuated FAP, and other polyposis syndromesHereditary non-polyposis colorectal cancer (Lynch syndrome)Synchronous colon tumors

Patients undergoing surgeries other than TME (e.g., partial mesorectal excision, rectosigmoid resection, end colostomy) will not be included in the study. Following data entry, patients for whom pathology reports indicate that TME was not performed or who has missing data regarding inclusion criteria will be excluded from the study. Patients who are unable to complete neoadjuvant therapy for any reason (such as toxicity, non-compliance, or accessibility issues) will not be excluded from the study. These patients will be evaluated within the neoadjuvant therapy group. Accordingly, when analyzing this aspect, an intention-to-treat analysis will be conducted without cross-over.

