### Statistical methods

During the study, missing data analyses and data quality assessments will be actively conducted, and measures to prevent data loss and enhance data quality will be implemented as appropriate. All statistical analyses will be conducted by experts from the TSCRS Biostatistics and Bioinformatics Analysis Unit using SPSS (SPSS Inc, Chicago, IL) software packages.

Multivariable regression analyses will be conducted to evaluate the effect of treatment strategy (direct TME vs. nCRT followed by TME) on the primary and secondary outcomes. The following covariates will be included in the models based on clinical relevance and literature review: age, sex, clinical T stage (cT2 vs. cT3), clinical N stage (N0 vs. N+), tumor differentiation, regimens of neoadjuvant treatment (long-course CRT, short-course RT, TNT with long or short-course RT), interval between neoadjuvant RT/CT and surgery, comorbidities (e.g., Charlson Comorbidity Index), performance status, postoperative complications (Clavien-Dindo), tumor histology, pathologic TME quality (pathologic completeness of the mesorectum), and center effect (as a random effect if appropriate).

For time-to-event outcomes such as disease-free survival (DFS) and overall survival (OS), Cox proportional hazards regression models will be used to estimate hazard ratios and 95% confidence intervals. The proportional hazards assumption will be tested using Schoenfeld residuals.

To address potential selection bias due to the non-randomized design, propensity score methods will be applied. Specifically, propensity scores for receipt of nCRT (vs. direct TME) will be estimated using logistic regression including the aforementioned covariates. The primary analysis will adjust for the propensity score as a covariate in the Cox model. Sensitivity analyses will be conducted using propensity score matching (1:1 nearest neighbor matching without replacement) and inverse probability of treatment weighting (IPTW) to ensure the robustness of results.

Patients lacking the main data specified in the inclusion and exclusion criteria, demographic data, or follow-up data related to the primary endpoint will be completely excluded from the study. Patients with missing data from other variables or secondary endpoints will only be excluded from those specific analyses, and secondary endpoints will be evaluated using data from patients with complete datasets.

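### Read literally, the nCRT definition admits patients given chemotherapy without radiation, which does not fit the stated contrast or the regimen list

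*Protocol article*

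**What the plan says.** All of the following is in the protocol article.

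- **Interventions, group labels.** The nCRT group is "Patients who receive nCRT prior to TME". The direct TME group is "Patients who undergo direct TME without neoadjuvant treatment". At the end of the study, "patients will be categorized into two groups based on whether they received nCRT".
- **Interventions, meaning of nCRT.** Neoadjuvant treatments "include all conventional chemoradiotherapy regimens or total neoadjuvant chemoradiotherapy regimens", followed by a parenthesis: "standard short or long course radiation and/or any standard chemotherapy regimen". The regimens must be ones described in the cited European and American guidelines.
- **Trial design.** The study is set up "with a comparative analysis between those receiving neoadjuvant chemoradiotherapy and those who do not".
- **Statistical methods.** The model covariates include "regimens of neoadjuvant treatment (long-course CRT, short-course RT, TNT with long or short-course RT" as the regimen categories.
- **Exclusion criteria.** Neoadjuvant immunotherapy is an exclusion; neoadjuvant chemotherapy alone is not listed. Of patients who cannot complete neoadjuvant therapy, the section says: "These patients will be evaluated within the neoadjuvant therapy group".

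**The concern.** The study asks whether chemoradiotherapy can be omitted. It assigns no treatment, so the rule that sorts patients into groups is what defines the exposure. The joining words in the parenthesis allow three cases: radiation with chemotherapy, radiation alone, and chemotherapy alone. The third involves no pelvic radiation, yet the patient would be analysed in the arm that stands for irradiated treatment.

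Two things could follow. On disease-free survival and local recurrence, patients without radiation in the nCRT arm could make the arms look more alike. The Discussion frames the aim as non-inferiority, so likeness favours the hoped-for conclusion. On LARS score and quality of life, the same mixing could blur the morbidity contrast that the Introduction gives as the reason for the study. Because patients are sorted at the end of the study, an unsettled rule might also be settled after outcomes are known.

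**Working it through.** **1. One patient, each rule.** Take an otherwise eligible patient who had preoperative chemotherapy, no pelvic radiation, then TME.

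| Rule | Where the patient falls |
|---|---|
| Parenthesis in Interventions, read literally | nCRT |
| Term that the parenthesis qualifies (chemoradiotherapy regimens) | Not nCRT on the ordinary meaning |
| Contrast in Trial design | Not a recipient of chemoradiotherapy on the ordinary meaning |
| Direct TME definition | Barred, having had neoadjuvant treatment |
| Regimen list in Statistical methods | No level; all levels contain radiotherapy |
| Exclusion criteria | Not excluded |

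The literal parenthesis conflicts with the Trial design contrast and with the regimen list. It does not conflict with the direct TME definition, which only keeps the patient out of that group.

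**2. The plan's own figure.** Sample size and recruitment gives 80% in both groups, α = 0.05, 80% power, 396 patients, then 436. It states neither a margin nor whether α is one-sided. With an assumed margin of 10 points and one-sided α of 0.05:

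n per group = (1.645 + 0.842)² × (0.80 × 0.20 + 0.80 × 0.20) / 0.10² = 6.18 × 32 ≈ 198, so 396 in total.

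198 × 1.10 = 217.8, so 218 per group and 436 in total. One-sided 0.025 with the same margin gives 504, which does not match. The definition of nCRT changes none of these figures. The 10 points is used below because it reproduces 396 and equals the difference named in the stopping rule.

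**3. Size if such patients are enrolled.** The document gives no chemotherapy-only share f, so 5–20% of the nCRT group is assumed. As a worst case, these patients are assumed to have the same outcomes as direct TME patients.

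- Affected patients = 218 × f.
- Apparent difference = true difference × (1 − f).
- False non-inferiority: the true rates are set at 80% with radiation and 70% for direct TME, a deficit equal to the assumed margin. The mixed nCRT arm has p = 0.80 − 0.10f. With 198 per group, SE = √[p(1 − p)/198 + 0.70 × 0.30/198], and the chance of declaring non-inferiority is Φ[(0.10 − (p − 0.70))/SE − 1.645].

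Example, f = 10%: p = 0.79, SE = √[(0.1659 + 0.21)/198] = 0.0436, and Φ(0.01/0.0436 − 1.645) = Φ(−1.415) ≈ 7.9%.

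**4. Cost of leaving them out.** If they are removed without replacement and both groups are truly at 80%, power = Φ[0.10/√(0.16/(198(1 − f)) + 0.16/198) − 1.645]. If they are replaced, 218/(1 − f) patients must be enrolled under the literal definition to reach 218.

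| f | Affected of 218 | A 10-point difference appears as | False non-inferiority | Power if left out, not replaced | Enrolled to reach 218 |
|---|---|---|---|---|---|
| 0% | 0 | 10.0 | 5.0% | 80.0% | 218 |
| 5% | 11 | 9.5 | 6.3% | 79.1% | 230 |
| 10% | 22 | 9.0 | 7.9% | 78.1% | 243 |
| 20% | 44 | 8.0 | 11.7% | 75.8% | 273 |

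**The case against.** A reader might infer that the protocol does place chemotherapy-only patients in the nCRT group, that this contradicts every other grouping rule, and that the comparison is therefore diluted. The document does not support that much.

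- **Intent.** The parenthesis explains a phrase about chemoradiotherapy regimens. Short-course RT appears in the regimen list and need not include chemotherapy, so the wording may be meant only to cover short-course radiation alone, or chemotherapy added in total neoadjuvant treatment. This is plausible. It is not stated, however, and centres have to apply the words they are given.
- **Contradiction.** If the literal parenthesis is taken as the definition of nCRT, sorting by receipt of nCRT follows it, and the direct TME rule is compatible. This stands. The mismatch is with the Trial design contrast, on its ordinary meaning, and with the regimen list.
- **Number of patients.** Regimens are limited to those in cited guidelines that are not at hand. There may be few such patients, or none.
- **Dilution.** The 5–20% share is assumed. The primary endpoint counts distant as well as local recurrence, and nothing in the document shows that chemotherapy-only patients would fare like direct TME patients. The calculation is a worst case.
- **Recoverability.** Radiotherapy and chemotherapy details are recorded, so these patients can be found. That makes the fix cheap, but it does not say which group they belong to.

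**Conclusion.** The point holds as an inconsistency in the definition of the exposure. As worded, the Interventions section can put patients without pelvic radiation in the nCRT arm, while Trial design and the regimen list describe an exposure that contains radiotherapy. These patients have no place in the direct TME group and no exclusion applies to them.

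The effect on results is conditional. It requires that such patients are enrolled and that they fare like non-irradiated patients. Under both conditions, the share of 5–20% and the margin and one-sided α assumed above, a 10-point difference appears as 9.5 to 8.0 points and false non-inferiority rises from 5.0% to between 6.3% and 11.7%. The direction favours a no-worse conclusion. The stated 396 and 436 are unaffected. This should be corrected, though it does not undermine the design.

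**What to change.** For the analysis groups, and without bearing on anyone's treatment:

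1. Define the nCRT group as patients whose neoadjuvant plan includes pelvic radiotherapy, with or without chemotherapy: long-course, short-course, or total neoadjuvant treatment with either. Keep patients who do not complete it, as the Exclusion criteria section already provides.
2. Leave patients given neoadjuvant chemotherapy without planned radiotherapy out of the primary two-group comparison. Keep them in the database, report them separately, and do not count them toward the 218 per group.
3. Reword the parenthesis in Interventions to radiation, with or without chemotherapy, so that it agrees with Trial design and the regimen list. Merely deleting the joining words would garble the sentence, and replacing them with a plain 'and' would drop short-course RT alone, which the regimen list includes.

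The cost is one or two sentences. Regimen details are already to be recorded, and the article says that recruitment had not begun, so the rule can be set before any outcome exists. The downside is that chemotherapy-only patients do not contribute to the primary comparison. Replacing them avoids the power loss shown above, at the price of somewhat more enrolment.

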#### Restaging.

Detailed data regarding the restaging process for patients receiving neoadjuvant treatment will be systematically recorded in the database. Specifically, the start and end dates of neoadjuvant treatments, as well as the dates of restaging MRI and CT scans, will be documented for each patient, in line with current clinical guidelines. The MRI will evaluate tumor regression, involvement of the mesorectal fascia, and nodal status, while the CT will assess for distant metastases. In this regard, variations between centers can also be evaluated as variables in the regression models during the final analysis.

#### Follow-up.

Although follow-up protocols may vary among participating centers, a standardized follow-up scheme will be implemented. All patients will be monitored at regular intervals postoperatively: every three months during the first two years, every six months from years three to five, and annually thereafter. Follow-up assessments will include physical examination, serum carcinoembryonic antigen (CEA) measurement, and imaging studies (chest and abdominal CT, pelvic MRI) as per standard rectal cancer surveillance guidelines. Patient-reported quality of life will be evaluated at 1, 3, and 5 years post-surgery. All follow-up data, including recurrence, survival, and functional outcomes, will be systematically collected and entered into the study database.

### Outcomes

#### Primary outcome measure.

3-year DFS: The proportion of patients who remain free of disease recurrence (local or distant) three years after surgical intervention. DFS will be assessed through clinical evaluations, imaging studies, and pathology reports at regular follow-up intervals.

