#### Secondary outcome measures.

5-year DFS: The proportion of patients who remain free of disease recurrence (local or distant) five years after surgical intervention.3- and 5-year Overall Survival: The proportion of patients alive at 3- and 5-years post-treatment, regardless of disease status.3- and 5-year Local Recurrence Rate: The percentage of patients experiencing tumor recurrence at the primary site (anastomosis or pelvis) within 3 and 5 years.1-, 3- and 5- year Colorectal Cancer Specific Quality of Life: Patient-reported outcomes assessed using the New Cleveland Clinic Colorectal Cancer Quality of Life Questionnaire [14].1-, 3- and 5- year Bowel Dysfunction Related Quality of Life: Patient-reported outcomes assessed using the low-anterior resection syndrome (LARS) score [15].

Fig 1 represents the timeline of anticipated recruitment and outcome measures.

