### Sample size and recruitment

The literature reports a mean 3-year disease-free survival rate of 75–85% for the sample to be included in the study [16]. For patients with mid-rectal tumors (cT2N+ and cT3N0) without high risk MRI findings, the 3-year disease-free survival rate was estimated to be 80% for both direct TME and TME following neoadjuvant chemoradiotherapy. Under these conditions, with α = 0.05 (95% confidence interval) and 80% power, the power analysis indicated that a total of 396 patients (1:1 ratio) would be required. Considering a 10% dropout rate, it is planned to include 218 patients in each group, for a total of 436 patients.

According to data from the Turkish Ministry of Health, General Directorate of Public Health, a total of 24,312 patients were diagnosed with rectal cancer between 2020 and 2024, of whom 17,896 underwent surgery (https://hsgm.saglik.gov.tr/tr/kanser.html). Since this study will be conducted nationally under the sponsorship of the main society of Turkish colorectal surgeons TSCRS, we anticipate reaching the targeted patient number within five years from the start of the study. To achieve this goal, TSCRS will utilize various channels, including mailing, social media, and its website, to announce the study and inform surgeons about the protocol.

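### The primary endpoint is called disease-free survival but is defined by recurrence alone, so a death without recurrence is never counted as a failure

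*Protocol article*

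**What the plan says.** Under Primary outcome measure, 3-year DFS is "The proportion of patients who remain free of disease recurrence (local or distant) three years after surgical intervention". The next sentence gives the sources of information: "DFS will be assessed through clinical evaluations, imaging studies, and pathology reports at regular follow-up intervals". Vital status is not among them.

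Under Secondary outcome measures, 5-year DFS has the same form: "The proportion of patients who remain free of disease recurrence (local or distant) five years after surgical intervention". Death enters only through overall survival: "The proportion of patients alive at 3- and 5-years post-treatment, regardless of disease status".

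Statistical methods treats DFS as a time-to-event variable: "For time-to-event outcomes such as disease-free survival (DFS) and overall survival (OS), Cox proportional hazards regression models will be used". It gives no event list and no rule for a patient who dies without recurrence. The same section says that patients lacking "follow-up data related to the primary endpoint will be completely excluded from the study".

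Deaths are collected. The Interventions section states "Routine follow-up information for all patients including morbidity, radiologic assessments, recurrence, mortality be recorded in the database", and the Follow-up section also lists survival among the data entered.

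The sample size rests on a rate labelled DFS: "3-year disease-free survival rate was estimated to be 80% for both direct TME and TME following neoadjuvant chemoradiotherapy".

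**The concern.** DFS ordinarily counts death from any cause as an event alongside recurrence. Here the label says survival and the definition says recurrence. This is not a detail left to an analysis plan: the article gives the definition twice, with the events listed in brackets, and death is not one of them.

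The question is whether omitting neoadjuvant chemoradiotherapy (nCRT) preserves DFS, in groups formed by clinical choice. The planned covariates include age, comorbidity and performance status, so the protocol itself allows that the groups may differ on factors that also drive death without recurrence. If deaths after surgery from complications, late toxicity or other illness differ between the groups, the primary comparison cannot register it, in either direction. The rule for terminating the study on a DFS difference of more than 10% (Adverse event reporting, safety and criteria for discontinuing) uses the same term and inherits the gap.

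**Working it through.** **1. What happens to a patient who dies without recurrence.** The text allows three readings:
- Proportion wording (Primary outcome measure): no recurrence has occurred, so the patient counts as recurrence-free.
- Cox model (Statistical methods) with the defined event, recurrence: the patient is censored at death.
- Exclusion rule (Statistical methods): the patient is removed if death before 3 years is taken as missing primary-endpoint follow-up. This is the least natural reading, because a recorded death is not obviously missing data.

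The protocol does not choose among them. In none of them is the death a failure.

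**2. Reproducing the planned 396.** Inputs from Sample size and recruitment: 80% in both groups, α = 0.05, power 80%, 1:1. No margin or sidedness is given there. The only between-group difference stated anywhere is the 10% in the termination rule, and non-inferiority is named only in the Discussion. With margin 0.10 and one-sided α of 0.05 (both inferred):

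n per arm = (1.645 + 0.842)² × 2 × 0.80 × 0.20 / 0.10² ≈ 197.8, rounded up to 198, or 396 in total.

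This matches the plan. One-sided 0.025 would give 504.

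**3. What the definition can hide.** The documents give no rate of death without recurrence, so the rates here are assumptions. Take 80% recurrence-free in both groups, with such deaths at 2% after nCRT and 6% after direct total mesorectal excision (TME):
- Recurrence-only endpoint: 80% versus 80%, difference 0.
- DFS including death: 78% versus 74%, difference 4 points, which is 4/10 = 40% of the inferred margin.
- Chance of declaring non-inferiority at 198 per arm, on the endpoint as defined: 80%.
- The same chance on DFS including death: Φ[(0.10 − 0.04)/√((0.78×0.22 + 0.74×0.26)/198) − 1.645] = Φ(1.399 − 1.645) ≈ 40%.

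With 2% versus 5% the hidden difference is 3 points and that chance is about 50%. With the imbalance reversed (5% after nCRT, 2% after direct TME), a 3-point advantage for direct TME is hidden and the chance is about 92%.

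**4. What the fix does to the sample size.** This depends on what the 80% measures.
- If it already includes deaths, 396 stands. Under the present definition, assumed deaths of 2% to 10% would mean about 9 to 44 of the 436 patients (436 × 0.02 = 8.7; 436 × 0.10 = 43.6) die without being counted as events.
- If it is recurrence-only, then DFS = 80% minus the deaths. Power at 198 per arm is Φ[0.10/√(2p(1−p)/198) − 1.645]:

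| Assumed deaths without recurrence, both groups | DFS (p) | Power at 198 per arm | Total for 80% power, before dropout |
|---|---|---|---|
| 2% | 78% | 77.5% | 426 |
| 3% | 77% | 76.4% | 438 |
| 5% | 75% | 74.3% | 464 |
| 8% | 72% | 71.6% | 500 |
| 10% | 70% | 70.1% | 520 |

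**The case against.** The best defence is that the endpoint is called survival, and that remaining free of disease at three years can be read as requiring the patient to be alive. The investigators may intend that. But the bracketed event list and the separate overall survival definition point the other way, and a primary endpoint should not depend on a charitable reading. What stands is that the handling of these deaths is left open: the protocol nowhere says that they count as successes.

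There is also partial mitigation. Overall survival at 3 and 5 years is a secondary outcome, so a mortality imbalance would be visible in the study, though not in the primary comparison. Age, comorbidity and performance status are model covariates. But adjustment does not turn an uncounted death into an event.

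Three stronger readings are tempting and are not supported:
- *That the 80% planning rate is for a different endpoint.* It comes from a cited source that is not at hand, and that source's DFS definition is unknown. The mismatch is possible, not shown.
- *That omitting deaths lowers the power of the Cox analysis.* At the plan's own 80%, 0.2 × 396 ≈ 79 events with HR = ln 0.70/ln 0.80 = 1.60 give about 67% power (one-sided 5%), but that is the full planned count, not one reduced by omitting deaths. If 5% die without recurrence and 85% are recurrence-free, 0.15 × 396 ≈ 59 events with the same 10-point margin (HR = ln 0.75/ln 0.85 = 1.77) give about 71%. Power falls only if the hazard ratio is held fixed.
- *That counting deaths would bring in all fatal chemoradiotherapy toxicity.* The clock starts at surgery, and the Inclusion criteria admit only patients who underwent TME. A death before surgery stays outside the comparison under either definition.

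**Conclusion.** The point holds and should be settled before recruitment starts. The primary endpoint's name and its stated definition disagree, and following the definition means that no death without recurrence is ever a failure. That rests on the text alone.

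The size of the effect is not known. It rests on assumed death rates, and the comparison with a 10-point margin rests on an inferred margin and an inferred one-sided 5% level. The 4-point example is therefore illustrative. The harm is limited to deaths after surgery, and it could favour either group. The documents do not show that 396 is wrong; they leave open whether the 80% matches the endpoint.

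**What to change.** - Define 3- and 5-year DFS as time from surgery to the first of local recurrence, distant recurrence or death from any cause. Censor event-free patients at their last disease assessment, and estimate by Kaplan-Meier and Cox regression.
- Keep recurrence alone as a secondary endpoint, with death as a competing event.
- State that a death before 3 years is an outcome and not missing follow-up under the exclusion rule.
- Apply the same definition wherever DFS is used, including the termination rule.
- Check the source of the 80% and say whether it includes deaths. If it is recurrence-only, restate the power or the sample size from the table above.

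The rewording costs little: mortality is already recorded, and the article states that recruitment had not begun. The possible real cost is in numbers. If the 80% is recurrence-only and 80% power is to be kept, the total before dropout rises from 396 to between 426 and 520 for assumed deaths of 2% to 10%.
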